### Overview of study design

2.1.

This Phase II RCT tests the effects of telephone-based ACT on patient fatigue interference and caregiver burden in advanced GI cancer. We plan to enroll 244 patient-caregiver dyads over about four years. Dyads are randomized to six weekly 50-min telephone sessions of ACT or six weekly 50-min telephone sessions of education/support. Outcomes are assessed at baseline, 2 weeks post-intervention, and 3 months post-intervention (primary endpoint). Dyads in both conditions also complete a 30-min booster phone session one month after the 2-week follow-up. This trial is registered in clinicaltrials.gov (NCT06532877) and approved by the Indiana University Institutional Review Board.

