#### Analyses of potential covariates

3.1.2.

*T*-tests and chi-square analyses will be used to examine differences between study conditions on potential baseline covariates (e.g., demographics, medical factors). Any differences will be considered when interpreting results, and factors that differ between groups will be included as covariates in sensitivity analyses.

### Analysis for aim 1

3.2.

Linear mixed effects modeling (R lme4) [66] will be used to test the hypothesis that ACT will improve the primary outcomes of patient fatigue interference and caregiver burden as compared to education/support. The model for each outcome will include the main effects of time (as categorical) and condition (ACT vs. education/support) and the time-by-condition interaction. Time will be dummy coded using two dummy variables, with baseline as the reference group. A treatment effect will be evidenced by a significant time-by-condition interaction. If the treatment effect is significant, follow-up tests (R emmeans) [67] will be performed to examine group differences at each follow-up.

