We estimated the effect size based on the difference between study conditions on the primary outcomes of patient fatigue interference and caregiver burden at 3 months post-intervention. In our pilot RCT in advanced GI cancer, at 3 months we found a medium effect (*d* = −0.60) of condition (ACT vs. education/support) on patient fatigue interference and a small effect (*d* = −0.18) of condition on caregiver burden [21]. In contrast to our pilot, the current trial has a booster session to maintain ACT’s effects. Minimal clinically important differences (MCIDs) or clinically meaningful changes on the Fatigue Interference subscale of the FSI have been reported for cancer populations (range = 0.39–1.63) [68]. MCIDs in caregiver burden have yet to be determined. Estimates of treatment effects from pilots are imprecise [69,70]; thus, we examined results across relevant ACT trials and recommendations regarding MCIDs [71,72] to inform our power calculation. Although ACT has rarely been studied with cancer caregivers, it had a medium effect (*d* = −0.39) on dementia caregivers’ depressive symptoms – which are strongly correlated with caregiver burden [73] – relative to psycho-education at 6 months post-intervention [74]. Additionally, ACT had medium to large effects on mental health outcomes in a meta-analysis of RCTs for clinical populations [75]. In the absence of an established MCID for a self-report measure, a standardized effect size of 0.30–0.50 is recommended to estimate the MCID [71,72]. Thus, we estimate a moderate effect size of *d* = −0.40 for both primary outcomes. With *N* = 170 dyads at 3 months post-intervention (assuming 30 % attrition), we will have 85 % power (α = 0.05, two-tailed) to detect a Cohen’s *d* = −0.40 in a linear mixed model. The estimated attrition is based on our pilot data [21] and survival rates in advanced GI cancer [76].

### Analysis for aim 2

3.3.

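### Efficacy is declared from the joint time-by-condition interaction over both follow-ups, although 3 months is the primary endpoint and the basis of the sample size, so a 2-week-only effect can meet the stated criterion

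*Protocol article*

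**What the plan says.** Section 2.1 (Overview of study design) gives one time point primary status: "Outcomes are assessed at baseline, 2 weeks post-intervention, and 3 months post-intervention (primary endpoint").

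The power paragraph of section 3.2 (Analysis for aim 1) follows that choice. The effect size is based on the "difference between study conditions on the primary outcomes of patient fatigue interference and caregiver burden at 3 months post-intervention". It is set at d = −0.40, and the 85% power refers to the 170 dyads expected at 3 months.

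The analysis paragraph of section 3.2 sets the decision rule. The model has condition, categorical time and their interaction. "Time will be dummy coded using two dummy variables, with baseline as the reference group". Then: "A treatment effect will be evidenced by a significant time-by-condition interaction". The time-specific comparisons come last and are conditional: "If the treatment effect is significant, follow-up tests (R emmeans) [67] will be performed to examine group differences at each follow-up".

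**The concern.** Three occasions coded by two dummies give two interaction terms: the difference between arms in change to 2 weeks, and the difference in change to 3 months. The interaction test asks whether either departs from zero. Nothing in the article requires a 3-month difference before a treatment effect is declared, and the follow-up tests do not single out 3 months. The named primary endpoint therefore does not decide the primary hypothesis.

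A transient effect is a realistic possibility here. Section 3.2 says a booster session was added, unlike in the pilot, to maintain the effect, so fading was on the designers' minds. The pilot's 3-month effect on caregiver burden was only d = −0.18. If the benefit is present at 2 weeks and gone by 3 months, the rule as written would still report a treatment effect.

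**Working it through.** **Inputs from the article.** 244 dyads randomised (section 2.1), taken as 122 per arm because allocation is balanced in blocks of 2 and 4 (section 2.4). 170 dyads at 3 months, so 85 per arm; 30% attrition; d = 0.40 in absolute value; two-sided α = 0.05; power 85% (section 3.2). Pilot retention at 2 weeks was 81% (Introduction), so 0.81 × 122 ≈ 99 per arm.

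**Assumptions, not in the article.** Equal SD at all times (set to 1), the same correlation r between any two times (0.3 to 0.7), monotone dropout.

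**The plan's own figure.** Attrition agrees: 244 × 0.70 = 170.8. For power, use Φ(d/SE − 1.96).
- Plain comparison, 85 vs 85: SE = √(2/85) = 0.153, 0.40/0.153 = 2.61, power 74%.
- Adjusted for baseline, r = 0.5: SE = √(2 × 0.75/85) = 0.133, 0.40/0.133 = 3.01, power 85%.
- Change from baseline: 83.0% at r = 0.60 and 87.6% at r = 0.65.

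So 85% is attainable, but it depends on an analysis form and a correlation that the article does not state.

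**The declared test against a 3-month test.** Let δ = (δ₁, δ₂) be the true differences between arms in change from baseline to 2 weeks and to 3 months, and C the covariance matrix of their estimates in the stated model with 122/99/85 per arm.
- Interaction (2 df): noncentrality λ = δ′C⁻¹δ, referred to F(2, 168).
- 3-month contrast (1 df): δ₂/√C₂₂, referred to t(168).

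At r = 0.5, C₁₁ = 0.01925, C₂₂ = 0.02147 and C₁₂ = 0.00915.

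For δ = (0.40, 0): λ = 0.16 × 0.02147 / (0.01925 × 0.02147 − 0.00915²) = 10.4. The interaction is significant in 82.5% of trials by the F reference and 83.2% by the large-sample chi-square. The 3-month contrast is significant in 5%. In 78% of trials the interaction is significant while the 3-month contrast is not.

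For δ₂ = 0.40: 0.40/√0.02147 = 2.73, so the 3-month contrast has 78% power.

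| True effect at 2 weeks, 3 months (SD) | r | Interaction (2 df) positive | 3-month contrast (1 df) positive |
|---|---|---|---|
| 0.40, 0 | 0.3 | 68% | 5% |
| 0.40, 0 | 0.5 | 83% | 5% |
| 0.40, 0 | 0.7 | 97% | 5% |
| 0.20, 0 | 0.5 | 28% | 5% |
| 0.40, 0.20 | 0.5 | 73% | 27% |
| 0.20, 0.40 | 0.5 | 68% | 78% |
| 0, 0.40 | 0.5 | 78% | 78% |
| 0.40, 0.40 | 0.3 | 71% | 64% |
| 0.40, 0.40 | 0.5 | 84% | 78% |
| 0.40, 0.40 | 0.6 | 91% | 86% |

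The gap in the first rows depends on r and on the size of the 2-week effect; its direction does not. The power comparison in the last rows goes either way.

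**The case against.** The best reply has four parts.

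*The 3-month result will be visible.* After a significant interaction, group differences are tested at each follow-up, so an absent 3-month difference would show. The stated hypothesis names no time point, and section 3.2 speaks of a treatment effect, not of trial success. This limits the harm. It does not change the stated criterion, which is met before the 3-month comparison is looked at.

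*The headline scenario is extreme.* It takes the full design effect at 2 weeks and exactly zero at 3 months. The article reports no 2-week effect, and the pilot's 3-month effects (−0.60 and −0.18) are not zero, though the article itself calls pilot estimates imprecise. This stands as a caution on size: with 0.20 SD at 2 weeks the figure at r = 0.5 falls to 28%. But exact zero is not needed: an effect that halves from 0.40 to 0.20 is declared in 73% of trials, against 27% for the 3-month contrast.

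*The interaction test is often stronger.* For an effect sustained at both follow-ups it has 84% power against 78% at r = 0.5. This stands. A reader might infer that the interaction rule always costs power for the 3-month question; the calculation does not support that. Of the patterns tried it loses for 0.20 rising to 0.40, ties for 0 then 0.40, and gains for a sustained effect.

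*There is no inflation of type I error.* A reader might infer two chances at 5% per outcome, one for each interaction coefficient. The text does not support this. It refers to one significant interaction, followed by separate tests at each follow-up if it passes, which describes a joint test with post hoc comparisons. With no effect at either follow-up, such a test keeps 5% per outcome.

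Nor can the point be left to an analysis plan that is not shown: the article states the rule, and the rule conflicts with the article's own primary endpoint.

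**Conclusion.** The point holds as a mismatch between the primary endpoint and the test that decides the primary hypothesis. Under the rule as written, an effect confined to 2 weeks can be declared a treatment effect: in 68% to 97% of trials for effects of 0.40 then 0 SD and r from 0.3 to 0.7, where a 3-month test would be positive in 5%. These figures rest on 122/99/85 per arm, equal SDs and a common correlation, none of which the article fully specifies. The point does not extend to a claim of inflated type I error or of a general loss of power. It is made for the two primary outcomes only; the dyadic models and Sidak adjustment of Aim 2 were not examined, so nothing is claimed about them.

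**What to change.** For each primary outcome, name the single condition contrast at 3 months as the primary test, taken from the same mixed model as the condition-by-3-month term (two-sided 0.05). Report its estimate and 95% CI whatever the interaction shows. Keep the 2-week contrast and the overall interaction as supportive analyses. Tie the stated 85% power to this contrast and state the correlation it assumes.

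The change is about one paragraph of text and needs no new data, but it has two costs. A 2-week-only effect can no longer be claimed as the primary result. Power is also somewhat lower than for the interaction test if the effect is equal at both follow-ups: in the model as written the contrast has about 78% power at r = 0.5 and 86% at r = 0.6, so 85% needs r of about 0.6. If baseline means are constrained equal between arms, it has about 86% at r = 0.5. The wording should be settled before outcomes are seen by arm; otherwise the choice of which result counts becomes discretionary.

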Linear mixed effects modeling (R lme4) [66] will be used to test the hypothesis that ACT will improve secondary outcomes as compared to education/support. For outcome measures that only patients or caregivers complete, models will include main effects of time (as categorical) and condition and the time-by-condition interaction. Treatment effects will be evidenced by a significant time-by-condition interaction. For outcomes reported by patients and caregivers, multilevel modeling for dyadic data will be used [77,78]. The model will include the main effects of time, condition, and social role (patient vs. caregiver) as well as all two and three-way interactions. The time x condition x role interaction will estimate the degree to which the treatment effect is different for patients and caregivers. The *p* values from the analyses will be adjusted using the Sidak approach to control for the familywise Type I error rate due to correlated multiple secondary outcomes. If treatment effects are significant, follow-up tests (R emmeans) [67] will be performed to examine group differences at each follow-up.

### Analysis for aim 3

3.4.

Cross-lagged panel models in Mplus [79] will be used to test the hypothesis that increases in psychological flexibility will mediate ACT’s effects on primary outcomes (patient fatigue interference and caregiver burden). Outcomes will be examined in separate models that include condition, the mediator (assessed at baseline and 2 weeks post-intervention), and the outcome at all time points. To evaluate model fit, we will use the comparative fit index (CFI) and the root mean square error of approximation (RMSEA), with CFI ≥0.95 and RMSEA ≤0.05 indicating close fit [80]. The indirect effect of condition on each outcome via psychological flexibility will be quantified using the product of the two relevant effects and tested using bootstrapped confidence intervals (CIs) accounting for nonnormality [81]. A total of 10,000 bootstrapped samples will be drawn, and the indirect effect will be considered statistically significant at *p* < .05 if the 95 % CI does not include zero.

### Analysis for aim 4

3.5.

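### The Aim 1 interaction tests the difference in change from baseline, but the follow-up tests compare visit means that still contain the chance baseline difference, and are planned only after a significant interaction

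*Protocol article*

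**What the plan says.** Section 3.2 (Analysis for aim 1) sets the model: "The model for each outcome will include the main effects of time (as categorical) and condition (ACT vs. education/support) and the time-by-condition interaction". On coding it says: "Time will be dummy coded using two dummy variables, with baseline as the reference group". No baseline covariate and no constraint to a common baseline mean is stated, so the condition main effect is a free baseline difference between the arms.

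The criterion for efficacy is: "A treatment effect will be evidenced by a significant time-by-condition interaction". The next step is conditional on it: "If the treatment effect is significant, follow-up tests (R emmeans) [67] will be performed to examine group differences at each follow-up".

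Section 3.3 repeats that step for the secondary outcomes: "If treatment effects are significant, follow-up tests (R emmeans) [67] will be performed to examine group differences at each follow-up".

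Section 2.1 fixes the time point that matters most: "Outcomes are assessed at baseline, 2 weeks post-intervention, and 3 months post-intervention (primary endpoint". The power paragraph in section 3.2 plans on the same time point. It begins "We estimated the effect size based on the difference between study conditions on the primary outcomes" and goes on to specify 3 months, d = −0.40, 170 dyads remaining after 30% attrition, and 85% power.

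**The concern.** With baseline as the reference visit, each interaction coefficient is the between-arm difference in change from baseline. The between-arm difference in estimated means at 3 months is the condition main effect plus the 3-month interaction coefficient. The two differ by exactly the observed baseline difference, which in a randomized trial is chance. The interaction test removes that imbalance; the follow-up test, read plainly, puts it back.

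Two things are at stake. A trial can pass its efficacy test and then present a non-significant difference at its own primary time point, or one moved up or down by baseline imbalance. And because the visit comparisons are planned only after a significant interaction, the article plans no 3-month comparison for a trial that misses it. That is when an estimate and interval are most needed to set against the range of clinically meaningful change quoted for the fatigue measure (0.39–1.63).

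**Working it through.** **Inputs from the article.** 244 dyads, taken as 122 per arm (1:1 inferred from block sizes of 2 and 4 and the stated aim of balance). 170 dyads at 3 months, so 85 per arm. d = 0.40, two-sided α = 0.05, power 85%.

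**Assumptions.** About 99 per arm at 2 weeks (the pilot's 81% × 122). The within-person correlation r is not given, so a range of 0.3 to 0.8 is used, equal between all visits. Outcome SD is 1, dropout is monotone, variances are known, and the effect is 0.40 at both follow-ups unless stated.

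**The plan's own figure.**
- Sample size: 170/0.70 = 243, in line with 244.
- Power from 3-month means alone, 85 per arm: SE = √(2/85) = 0.153; 0.40/0.153 = 2.61; power = Φ(2.61 − 1.96) = 74%.
- Baseline-adjusted with r = 0.5: SE = 0.153 × √(1 − 0.25) = 0.133; 0.40/0.133 = 3.01; power = 85%.
- The two-degree-of-freedom interaction test with 122/99/85 per arm and r = 0.5: 84.9%.

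So 85% is reproduced, given a correlation of about 0.5.

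**Gap between the two contrasts.** The SD of the chance baseline difference is √(2/122) = 0.128, and 0.128/0.40 = 0.32, about a third of the planned effect. Both contrasts averaged 0.40 in simulation.

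**Precision at 3 months.** Generalized least squares for the stated model (information summed over the dropout patterns, then inverted) gives the SE of the group difference as 0.1508 at r = 0.3 and 0.1465 at r = 0.5. Its covariance with the baseline difference is r × 2/122, where 2/122 = 0.01639. Hence:
- variance of the change contrast = variance of the group difference + 0.01639 × (1 − 2r)
- variance with a common baseline = variance of the group difference − 0.01639 × r²

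| | r = 0.3 | r = 0.5 |
|---|---|---|
| Group difference: variance, SE, power | 0.02273, 0.1508, 76% | 0.02147, 0.1465, 78% |
| Change contrast: variance, SE, power | 0.02929, 0.1711, 65% | 0.02147, 0.1465, 78% |
| Common baseline: variance, SE, power | 0.02125, 0.1458, 78% | 0.01737, 0.1318, 86% |

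Each power is Φ(0.40/SE − 1.96).

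**How often the steps disagree.** 400,000 simulated trials per setting, d = 0.40 at both follow-ups:

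| r | Interaction significant | 3-month group difference non-significant, given a significant interaction |
|---|---|---|
| 0.3 | 72% | 19% |
| 0.5 | 85% | 19% |
| 0.7 | 97% | 18% |
| 0.8 | 99.7% | 17% |

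**Sensitivity of that last column (r = 0.3 to 0.7).**
- d = 0.20 at both visits: 52–61%
- d = 0.60 at both visits: 1–2%
- d = 0.20 at 2 weeks and 0.40 at 3 months: 10–15%
- d = 0.40 with only 85 per arm at every visit: 20–25%

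**After replacing the follow-up with the 3-month change contrast.** Given a significant interaction, that contrast is still non-significant in 17% (r = 0.3), 12% (r = 0.5) and 4–5% (r = 0.7). This remainder is the ordinary behaviour of a two-degree-of-freedom test followed by a one-degree-of-freedom contrast.

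**The case against.** A reader might infer that the reported 3-month effect is not the effect that was tested. The article does not support that. Under randomization the two contrasts have the same expected value, and a group difference at 3 months is the quantity on which the trial was sized. Nor are these raw means: emmeans returns marginal means from a mixed model fitted to all randomized participants, with incomplete cases kept.

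A reader might also infer that nothing says which result governs, or that a trial missing its interaction test would report no 3-month difference at all. Section 3.2 names the interaction as the evidence of efficacy. What it makes conditional is follow-up tests, not the reporting of estimates, and the fitted model yields the 3-month difference in change and its standard error whatever the p value. The chance of missing the interaction test is therefore not a measure of this defect.

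Finally, emmeans can be told to contrast changes, the wording does not rule that out, and an article may leave exact contrasts to the full protocol or analysis plan. Testing an interaction and then comparing groups at each visit is also common practice.

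Most of this stands, and it limits the point. But the article does not merely omit the contrast. It states a rule which, read plainly, takes the primary time point from a contrast not adjusted for baseline, although the test that opens it removes baseline imbalance. It also states that the comparison waits on an omnibus result. Both can be corrected in this text.

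**Conclusion.** The point holds as a mismatch of estimator and test, with the same target effect. At the design effect of d = 0.40, with 122/99/85 per arm and r between 0.3 and 0.8, about 17–19% of trials that pass the interaction test would show a non-significant 3-month group difference. The gap between the two 3-month estimates has SD 0.128.

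The rate is not a fixed property of the plan. It moves with the unstated correlation, the true effect and retention, as the sensitivity results show. Part of it comes from following a two-degree-of-freedom test with a single contrast, and would remain after any change of contrast. The planned conditional reporting of the primary time point is a separate weakness that does not depend on these assumptions. Neither invalidates the trial; both are worth settling before unblinding.

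**What to change.** Make the follow-up contrasts baseline-consistent with the test that precedes them. There are two ways:

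1. Define them as the interaction contrasts, that is, the between-arm difference in change from baseline at 2 weeks and at 3 months.
2. Preferably, use one baseline-adjusted or common-baseline model for both the overall test and the visit contrasts. This avoids the precision that change contrasts lose at low correlation: 3-month power is 78% against 65% at r = 0.3, and 86% against 78% at r = 0.5.

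State that the 3-month and 2-week contrasts will be reported with 95% CIs whatever the interaction p value, and apply the same wording to Aim 2. It would help to give the within-person correlation behind the 85% power.

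The cost is a line of code and a wording change, with no new data. The overall test and the 3-month contrast can still disagree, so the text should keep saying which of them decides efficacy.

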### Randomization and blinding

2.4.

Following baseline assessments, dyads are randomly assigned to ACT or education/support using stratified block randomization to balance the groups by patient age (<65 yrs. vs. ≥65 yrs.) and performance status (patient-reported ECOG scores 0 or 1 vs. 2 [28]). Performance status informs treatment decisions for advanced GI cancer [33]. The statistician uses the R package “blockrand” [34] to generate random assignments within blocks. Randomly varying block sizes of 2 and 4 are used to maintain allocation concealment and ensure balanced allocation to study conditions. Following randomization, study condition assignments are identifiable to participants, interventionists, their supervisors, and staff mailing intervention materials. Other investigators, outcome assessors, and data analysts are blinded.

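### The aim 1 model lets baseline means differ by arm although dyads are randomized after baseline; a common baseline mean would add about 8 points of power at 3 months (r = 0.5) at no cost

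*Protocol article*

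**What the plan says.** - **Timing.** Section 2.4: "Following baseline assessments, dyads are randomly assigned to ACT or education/support". Section 2.1 names 3 months post-intervention as the primary endpoint.
- **Model.** Section 3.2: "The model for each outcome will include the main effects of time (as categorical) and condition (ACT vs. education/support) and the time-by-condition interaction". Time is categorical, with two dummy variables and baseline as the reference. A significant interaction counts as a treatment effect. If it is significant, emmeans tests compare the arms at each follow-up.
- **Power.** Section 3.2: "We estimated the effect size based on the difference between study conditions on the primary outcomes" at 3 months, and "Thus, we estimate a moderate effect size of *d* = −0.40 for both primary outcomes". With "170 dyads at 3 months post-intervention (assuming 30 % attrition"), the plan states "we will have 85 % power (α = 0.05, two-tailed") in a linear mixed model.
- **Enrolment.** Section 2.1: "We plan to enroll 244 patient-caregiver dyads over about four years".

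The article gives no correlation between repeated measures, no expected effect at 2 weeks, and no statement of which contrast was powered.

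**The concern.** With baseline as the reference time, the condition main effect is the difference between arms at baseline. The interaction terms are then differences in change from baseline. Randomization after baseline makes the expected baseline difference zero, so the model spends information on a quantity already known.

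Two things follow. The deciding test is less precise than it could be with the same data, in a trial that expects to lose 30% of its dyads. In addition, the emmeans comparisons at each follow-up are differences between arm means. They include any chance imbalance at baseline, while the interaction subtracts it. The gate and the tests behind it therefore estimate the effect in two ways and need not agree.

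**Working it through.** **Inputs.** From the article: 244 dyads, 30% attrition, d = 0.40, two-sided 0.05. 244 × 0.70 = 170.8, which agrees with the stated 170. Allocation is taken as 1:1, giving 122 per arm at baseline and 85 at 3 months. Assumptions: SD 1, compound symmetry with correlation r from 0.3 to 0.7, and 85 per arm (70%) or 99 per arm (the pilot's 81%) at 2 weeks.

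**Step 1: the plan's figure from its printed inputs.** A plain 3-month comparison has SE = √(2/85) = 0.153, and 0.40/0.153 = 2.61. Power = Φ(2.61 − 1.96) = 74.1% (73.7% by the t-test). So 85% needs a further assumption about the repeated measures.

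**Step 2: the 3-month contrast under the two models.** With 122 per arm at baseline and 85 at both follow-ups, the variances have a closed form:
- baseline means free: 2[(1 − r²)/85 + (1 − r)²/122]
- common baseline mean: 2(1 − r²)/85

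The extra term, 2(1 − r)²/122, is the price of estimating the baseline difference. At r = 0.5:
- free: 2[0.75/85 + 0.25/122] = 0.02175, SE 0.1475, power 77.4%
- common: 2 × 0.75/85 = 0.01765, SE 0.1328, power 85.3%

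The same calculation by generalized least squares, with the range covering 85 or 99 per arm at 2 weeks:

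| r | Baseline means free (as specified) | Common baseline mean |
|---|---|---|
| 0.3 | 64-65% | 78% |
| 0.4 | 70-71% | 81-82% |
| 0.5 | 77-78% | 85-86% |
| 0.6 | 85-86% | 90-91% |
| 0.7 | 93-94% | 95-96% |

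**Step 3: the deciding test.** The interaction has 2 degrees of freedom, so its power also depends on the effect at 2 weeks. At r = 0.5 with all available data and d = 0.40 at 3 months:

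| d at 2 weeks | Baseline means free | Common baseline mean |
|---|---|---|
| 0.40 | 82-85% | 92-95% |
| 0.20 | 68-69% | 79-80% |
| 0 | 79% | 82% |

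**Step 4: where the specified model reaches 85%.** The 3-month contrast does so at r of about 0.59-0.60. The 2-df test does so at r of about 0.50-0.54 if d = 0.40 at both follow-ups.

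**Step 5: the follow-up tests.** Under the free model, the 3-month difference from emmeans equals the interaction contrast plus the estimated baseline difference. With 122 per arm that difference has a standard error of √(2/122) = 0.128 SD, about a third of the planned effect (0.128/0.40 = 0.32). Under a common baseline mean the two coincide.

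**The case against.** A reader might infer that the 85% was calculated for a baseline-adjusted comparison, that the specified test really has 74-78%, and that the trial is therefore underpowered. The document does not support this. A baseline-adjusted comparison does give about 85% at r = 0.5, but that correlation comes from working backwards from the result. Other routes arrive at the same figure. With 122, 99 and 85 per arm, r = 0.5 and d = 0.40 at both follow-ups, the specified 2-df test itself has 84.9% power. The 3-month contrast as specified reaches 85% at r of about 0.60. The 74-78% describes a single-degree-of-freedom contrast at one assumed correlation, whereas the plan decides on the 2-df interaction. No printed calculation fails, and a condensed article may leave the correlation and the 2-week effect to the full protocol or SAP.

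It is also fair to say that a free-baseline mixed model is unbiased under randomization and keeps its type I error, and that the emmeans tests come only after a significant interaction, so they do not decide efficacy.

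All of this stands. It removes the charge of a power error. It does not remove the inefficiency, because the model and the decision rule are fixed in section 3.2, and the common-baseline model was more powerful for the 3-month contrast at every correlation examined.

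**Conclusion.** The aim 1 analysis is valid but gives up precision for no benefit. For the 3-month contrast the loss is about 11 points of power at r = 0.4, 8 at r = 0.5 and 5 at r = 0.6. For the 2-df interaction at r = 0.5 with d = 0.40 at both follow-ups it is about 10 points. These sizes rest on compound symmetry, 1:1 allocation, the attrition pattern above and correlations that are assumed, not taken from the article.

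The stated 85% is neither confirmed nor refuted. It is attainable under the specified model if r is about 0.6, or if r is about 0.50-0.55 and the full effect is already present at 2 weeks. It is not reached at r = 0.5 if the 2-week effect is smaller, for example 68-69% with d = 0.20 there. This is a free improvement to the plan, not a defect that must be repaired before the trial can be relied on.

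**What to change.** 1. In the aim 1 model, constrain the baseline means to be equal across arms: drop the condition main effect at baseline and keep condition-by-time at both follow-ups. Alternatively, model the two follow-ups with baseline score-by-time as a covariate. The first form keeps dyads with baseline data only in the likelihood, which suits the intent-to-treat and FIML statements in section 3.1.1.
2. Take the 2-week and 3-month differences from that same model, so that the deciding test and the follow-up comparisons concern the same quantities.
3. State the correlation, the assumed 2-week effect and the contrast on which the 85% rests.

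The cost is one changed line of model code and a few sentences in the SAP, made before the analysts see outcomes by arm. It needs no further dyads, assessments or data.
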